**Trial registration:**

This trial was registered on 3 December 2022, in the Chinese Clinical Trial Registry (http://www.chictr.org.cn), ChiCTR2200066381. The protocol version is V1.0 (20221104).

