### Outcome measures

All blood samples will be collected on PODs 1, 2, 3, 4, 5, 6, and 7 following the same procedure for performing serial laboratory evaluation. All blood samples will be collected at 7 a.m. every day, which then will be sent by the outcome assessor to the Department of Experimental Medicine for examining by a fixed physician. Preoperative laboratory parameters are viewed as baseline of postoperative laboratory parameters (if the postoperative stay is not more than 7 days, outcome assessors will be responsible for the subjects for blood sample collection).

Primary outcomes are as follows: peaks value of ALT and AST and AUC of ALT and AST.

Indicators of hepatocellular injury are as follows: ALT and AST of postoperative 7-day both the two groups; then, we will calculate the mean for postoperative 7-day after surgery to depict the line charts with mean ± stand error.

Peak values of ALT and AST as well as AUC values of the postoperative 7-day course of ALT and AST (peak value is defined as the maximum value measured in 7 days, and AUC is calculated by the value of postoperative 7 days). The magnitude of the effect of glucocorticoids on relieving surgical pressure and alleviating ischemia-reperfusion injury are assessed by the AUC surrounded by continuous ALT and AST, which is the metrics for declaring superiority of the tested intervention.

We decided that peaks value of ALT and AST and AUC of ALT and AST were primary outcomes after 16 July 2023.

Secondary outcomes:Intraoperative blood lossLiver function: assessed by measuring serum level of TBil and INR for coagulationInflammatory cytokines: assessed by IL-6, PCT, CRP, and their respective peaksPostoperative complications: according to the Clavien–Dindo grade, including major complications and minor complicationsPostoperative hospital staysMortality: defined as in-hospital death or death within 30 or 90 days after surgery

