### Statistical analysis

The trial is designed to test the superiority of dexamethasone to placebo with respect to the primary outcomes and secondary outcomes with the use of difference analysis. Superiority with respect to the primary outcomes are required before the secondary outcomes could be tested. All included participants will provide 80% power to detect superiority with respect to the primary outcomes. The AUC of ALT and AST will be tested for superiority, analyzed by Student’s *T* test or the Mann-Whitney *U* test.

Continuous variables will be presented as the mean ± standard deviation or median with its range based on normality testing and compared by an independent sample Student’s *T* test or the Mann-Whitney *U* test. Categorical variables will be presented as number (percentage) and compared using chi-square test or Fisher exact test. The modified intention-to-treat (ITT) principled analysis is applied for allocating patients into the group; moreover, when compliance is at a low level or the trial is no longer double-blinded, the as-treated (AT) analysis will be added to be supplements. Sensitivity analysis of missing data (loss to follow-up, death, withdrawal, etc.) will be conducted with the multiple-imputation approach. All tests for differences except primary outcomes are two-tailed and considered statistically significant if *P* values < 0.05. Bonferroni correction will be performed to correct for four primary outcomes statistically. We have changed the adjustment for multiple testing after 16 July 2023. All statistical analyses are performed by the SPSS version 20 and GraphPad Prism version 8.0.1.

As appropriate, the significance of postoperative categorical complications will be analyzed using chi-square test or Fisher exact test or will be tabulated and summarized using descriptive statistics.

Besides, according to the extent of resection and background of hepatic fibrosis after surgery, subgroup analysis will be performed to assess the protective effect of administration of dexamethasone before clamping the hilar pedicle on residual liver injury after undergoing liver resection with 25-min hepatic inflow occlusion.

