### Trial status

The trial has been reviewed and approved by the Biomedical Ethics Review Committee of West China Hospital, Sichuan University, on 28 November 2022 (ethics reference: 2022(1757)). The protocol version is V1.0 on 4 November 2022. This trial began to recruit patients on 3 December 2022. Recruitment was complete on 1 April 2023. Follow-up of all patients was complete on 1 July 2023. The data were unblinded on 16 July 2023. The final version of this protocol has been submitted for publication on 19 November 2023.

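### The four primary outcomes were decided, and the multiplicity adjustment changed, after unblinding, yet the article presents their tests as the designed confirmatory analysis

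*Protocol article*

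**What the plan says.** All statements are in the protocol article.

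- **Outcome measures:** "We decided that peaks value of ALT and AST and AUC of ALT and AST were primary outcomes after 16 July 2023".
- **Statistical analysis:** "Bonferroni correction will be performed to correct for four primary outcomes statistically", followed shortly by "We have changed the adjustment for multiple testing after 16 July 2023".
- **Trial status:** recruitment ended on 1 April 2023 and follow-up on 1 July 2023. Then: "The data were unblinded on 16 July 2023".
- **Statistical analysis, on the standing of these tests:** "The trial is designed to test the superiority of dexamethasone to placebo with respect to the primary outcomes and secondary outcomes", and "Superiority with respect to the primary outcomes are required before the secondary outcomes could be tested".
- **Trial registration and Trial status:** the only numbered version is V1.0 of 4 November 2022. Trial status also mentions a final version, submitted for publication on 19 November 2023, without giving it a number.

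The abstract lists the transaminase peaks and AUCs as primary endpoints and does not mention when they were chosen. The article does not give the primary outcome or outcomes, or the multiplicity rule, that applied before 16 July 2023.

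**The concern.** A confirmatory test needs its outcome family and its error-rate rule to be settled before anyone can know how the arms compare. Here both were settled when every outcome had been collected and allocation was open. A Bonferroni factor of four pays for testing the four outcomes that were kept. It does not pay for deciding, with allocation known, which outcomes form the family or what threshold each must meet.

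Two claims depend on that prespecification: the superiority claim on the primary outcomes, and the gate that lets the secondary outcomes be tested only if the primary ones succeed. If the family is post hoc, neither claim has the error control that the Statistical analysis section implies.

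**Working it through.** **1. Order of events**

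| Event | Date | Section |
|---|---|---|
| Protocol V1.0 | 4 November 2022 | Trial registration, Trial status |
| Follow-up complete | 1 July 2023 | Trial status |
| Data unblinded | 16 July 2023 | Trial status |
| Four primary outcomes decided | after 16 July 2023 | Outcome measures |
| Multiplicity adjustment changed | after 16 July 2023 | Statistical analysis |
| Final version submitted | 19 November 2023 | Trial status |

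Both decisions fall after unblinding, and more than eight months after V1.0. The point rests on this table alone.

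**2. What the sample size shows about the earlier plan**

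Inputs from the Sample size section: SD of peak ALT 184.684, target difference 58.882, one-sided 5% (1.645), 80% power (0.84), dropout about 10%.

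n per group = 2 × [184.684 × (1.645 + 0.84) / 58.882]² = 121.5, and 121.5 / 0.9 = 135.0.

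The stated 135 per group is reproduced. It rests on one outcome, peak ALT, at an undivided one-sided 5%. Peak AST was considered and needs fewer patients. No calculation is given for the AUCs, which Outcome measures nevertheless names as the measure for declaring superiority.

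The article therefore leaves room for at least three primary families: peak ALT alone at 0.05; the two AUCs, at 0.05/2 = 0.025 each if Bonferroni were applied; or all four at 0.05/4 = 0.0125 each. It does not say which applied before unblinding.

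**3. What Bonferroni over four covers**

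If the family was fixed without knowledge of the results, the familywise error is at most 4 × 0.0125 = 5%, and 1 − (1 − 0.0125)⁴ = 4.9% under independence.

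**4. Illustration of what it does not cover**

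Assume that the family was selected on results, that k candidate outcomes are independent, and that there is no true effect. The chance that at least one candidate passes 0.0125 is 1 − (1 − 0.0125)^k.

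- k = 4, only these four: 4.9%
- k = 6: 7.3%
- k = 9, all postoperative laboratory parameters listed under Data collection: 10.7%

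Correlation lowers these figures. With normal test statistics, an assumed common correlation ρ and c = 2.2414 (the one-sided 0.0125 point), the chance for k = 9 is 1 − ∫ φ(z) Φ[(c − √ρ z)/√(1 − ρ)]⁹ dz. This gives 9.1% at ρ = 0.3, 7.5% at ρ = 0.5 and below 6% at ρ = 0.7. The article gives no correlations, but peak and AUC of one enzyme come from the same seven daily values, so independence is an extreme case.

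**The case against.** Five counter-arguments deserve weight.

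- **The timing is disclosed.** The article gives the dates openly in three sections, so a reader might infer concealment only by overlooking them. What is missing is the label and its consequence for the superiority and gatekeeping claims.
- **The four outcomes look like a natural set.** They are every transaminase summary in the Data collection list (peak and AUC, ALT and AST), and the sample size already used the peaks. This makes a free pick from a wide pool less plausible. It does not show which outcomes were primary before unblinding.
- **The change may have been conservative.** The rule is said to have been changed, so an earlier one may have existed. If that was the undivided 5% of the Sample size section, Bonferroni made each test stricter. The direction of any bias is therefore unknown.
- **A later version exists.** Trial status mentions a final version, so the article does not pass off its whole text as V1.0. The fair remark is that this final version has no number and no list of changes.
- **V1.0 is not shown.** It may already have named some of these outcomes, or may not have fixed a primary outcome at all. A repair cannot presume its content.

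A stronger reading is tempting: that the investigators looked at the comparison and kept what worked, or that the true error rate is 10% or more. The article supports neither. It says that the data were unblinded, not that comparative results had been seen, and every inflation figure rests on an assumed candidate pool. All five arguments limit the size of the point. None restores prespecification.

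**Conclusion.** The point stands as one of timing and labelling. By the article's own dates, the primary family was decided and the multiplicity adjustment changed after unblinding, and the resulting tests are still presented as the designed superiority test with Bonferroni control and a gate. That control is not established.

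The size and direction of any bias cannot be determined from the document. The illustrative range runs from 5% or less, if the pool was only these four, to 10.7% for nine independent candidates with results-driven selection. It is not an estimate of what happened.

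The 80% power statement is a separate matter. It was derived at an undivided 5% and neither supports nor weakens this conclusion.

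**What to change.** 1. State the primary outcome or outcomes and the multiplicity rule in force before unblinding, whether in V1.0 of 4 November 2022 or in any later version that predates 16 July 2023. Make that analysis the sole confirmatory one.
2. Label every outcome or adjustment added after 16 July 2023 as post hoc. Report it with estimates and confidence intervals, without a superiority claim and without gatekeeping.
3. If no primary outcome or rule was fixed before unblinding, present all of these analyses as exploratory.
4. Give the final version a number and date, list the old and new text, and state which roles had access to unblinded data when the change was made.

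The cost is text and relabelling, with no new patients or data. The downside is that the confirmatory claim may become less favourable.

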### Safety and participant compensation

Although our intervention is convenient and less harmful, participants will be monitored for postoperative complications depicted in confirmed consent. We will care about patient and record each treatment until the AE is resolved. A participant who is found to be at risk to him/herself or others, or who has a SAE, will be referred to the relevant clinical services. Assessing the severity of the AE, SAE will be reported to the Biomedical Ethics Committee of West China Hospital, Sichuan University, within 24 h.

### Sample size

This trial is originally conceived by the statistical and clinical teams with a total of 270 patients (135 within each group). It is based on our previous RCT [10] and the other relative RCT in our center [27]. In our previous study, the standard deviation (*σ*) of the postoperative serum peak ALT value is 184.684, AST value is 141.1 between two groups, and the target difference (*δ*) is 58.882 IU/L. The sample size calculated using peak ALT value is larger than using peak AST value. Thus, we estimate a sample size of 135 patients in each group to achieve an 80% statistical power (Uβ = 0.84, 1-sided test) at the 5% significance level (Uα = 1.645, 1-sided test) as well as an estimated dropout rate of approximately 10%.

### Data management

Data will be recorded on case report form (CRF) in a timely, complete, and accurate manner by trained outcome assessors. CRF forms will be checked between outcome assessors. Then, they will input data into Excel software for the first time. Finally, another will input data for the second time; if the data is consistent, it can be submitted. Thus, electronic data will be stored and available to the outcome assessors only. Only they will have access to the data at the end of the RCT. Statistical analysis is conducted only after the trial. The Biomedical Ethics Committee of West China Hospital, Sichuan University, is responsible for monitoring the safety and process of the study.

### Statistical analysis

The trial is designed to test the superiority of dexamethasone to placebo with respect to the primary outcomes and secondary outcomes with the use of difference analysis. Superiority with respect to the primary outcomes are required before the secondary outcomes could be tested. All included participants will provide 80% power to detect superiority with respect to the primary outcomes. The AUC of ALT and AST will be tested for superiority, analyzed by Student’s *T* test or the Mann-Whitney *U* test.

Continuous variables will be presented as the mean ± standard deviation or median with its range based on normality testing and compared by an independent sample Student’s *T* test or the Mann-Whitney *U* test. Categorical variables will be presented as number (percentage) and compared using chi-square test or Fisher exact test. The modified intention-to-treat (ITT) principled analysis is applied for allocating patients into the group; moreover, when compliance is at a low level or the trial is no longer double-blinded, the as-treated (AT) analysis will be added to be supplements. Sensitivity analysis of missing data (loss to follow-up, death, withdrawal, etc.) will be conducted with the multiple-imputation approach. All tests for differences except primary outcomes are two-tailed and considered statistically significant if *P* values < 0.05. Bonferroni correction will be performed to correct for four primary outcomes statistically. We have changed the adjustment for multiple testing after 16 July 2023. All statistical analyses are performed by the SPSS version 20 and GraphPad Prism version 8.0.1.

As appropriate, the significance of postoperative categorical complications will be analyzed using chi-square test or Fisher exact test or will be tabulated and summarized using descriptive statistics.

Besides, according to the extent of resection and background of hepatic fibrosis after surgery, subgroup analysis will be performed to assess the protective effect of administration of dexamethasone before clamping the hilar pedicle on residual liver injury after undergoing liver resection with 25-min hepatic inflow occlusion.

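### The 80% power is claimed for the primary outcomes as a group, but only peak ALT was sized, at an unadjusted one-sided 5% level; nothing printed supports the figure for the AUC of ALT and AST

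*Protocol article*

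**What the plan says.** Three sections of the protocol article bear on this.

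- **Sample size.** The inputs are SDs of peak values ("of the postoperative serum peak ALT value is 184.684, AST value is 141.1 between two groups") and one target difference of 58.882 IU/L. Peak ALT was taken as the basis because "The sample size calculated using peak ALT value is larger than using peak AST value". The plan enrols 135 per group "to achieve an 80% statistical power (Uβ = 0.84, 1-sided test") "at the 5% significance level (Uα = 1.645, 1-sided test"), allowing about 10% dropout.
- **Outcome measures.** Four primary outcomes are listed: the peaks and the AUCs of ALT and AST. The AUC of the two enzymes is then singled out as the measure "which is the metrics for declaring superiority of the tested intervention".
- **Statistical analysis.** The section states that "All included participants will provide 80% power to detect superiority with respect to the primary outcomes" and continues that "The AUC of ALT and AST will be tested for superiority". It makes secondary testing conditional on superiority for the primary outcomes and applies Bonferroni correction across the four. By implication the primary tests are one-sided, since all other tests are said to be two-tailed.

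**The concern.** A power figure belongs to one statistic, one assumed effect and one significance level. Here it was derived for the peak of one enzyme and then stated for four outcomes, two of them on another scale. A peak is a single maximum in IU/L. A 7-day AUC accumulates seven correlated daily values, and Data collection lists it in different units. Its standardised effect depends on how long the drug effect lasts over the week and how strongly the days correlate, so neither the 58.882 IU/L nor the 80% carries over.

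What is at stake is interpretation. If an AUC comparison is null, a reader relying on the stated power would take it as the result of a test with 80% power, and nothing in the document supports that. Superiority on the primary outcomes also opens the secondary tests, so the stated power colours how the whole hierarchy is read.

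**Working it through.** **Inputs (Sample size section).** SD of peak ALT 184.684; SD of AST 141.1; difference 58.882 IU/L; z = 1.645 and 0.84; dropout 10%. From Statistical analysis: Bonferroni over four outcomes, so 0.05/4 = 0.0125 per test. The section does not print this level; it follows from the stated rule. Powers below use the normal approximation.

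**1. Reproduce the printed sample size.**
n = 2 × (1.645 + 0.84)² × (184.684/58.882)² = 121.5 per group; 121.5/0.9 = 135.0. The printed 135 comes from peak ALT with nothing else behind it.

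Peak AST with the same difference: 2 × (2.485)² × (141.1/58.882)² = 70.9 per group. The statement that ALT needs more patients than AST is correct, but it compares the two peaks only.

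**2. Power for peak ALT.**
Standardised effect = 58.882/184.684 = 0.319. Evaluable per group after dropout: 135 × 0.9 = 121.5, taken as 121.
Power = Φ(0.319 × √(121/2) − z) = Φ(2.480 − z).
- One-sided 0.05: Φ(2.480 − 1.645) = 79.8%.
- One-sided 0.0125: Φ(2.480 − 2.241) = 59.4%.

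An exact noncentral-t calculation gives 79.6% and 58.9%.

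**3. Power for AUC.**
This cannot be computed, because no AUC SD and no AUC difference are given. What can be computed is the standardised effect that would be detectable with 80% power:
- One-sided 0.05: (1.645 + 0.842) × √(2/121) = 0.320 SD.
- One-sided 0.0125: (2.241 + 0.842) × √(2/121) = 0.396 SD (0.395 with 122 per group).

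**4. Range over assumed AUC effects (121 per group, one-sided).** The effects in the first column are assumptions, not figures from the document.

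| Assumed AUC effect (SD) | Power at 0.05 | Power at 0.0125 |
|---|---|---|
| 0.20 | 46% | 25% |
| 0.25 | 62% | 38% |
| 0.30 | 75% | 54% |
| 0.35 | 86% | 68% |
| 0.40 | 93% | 81% |

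At the level used for sizing, the plausible values fall on both sides of 80%. The 80% applies to AUC only if its standardised effect happens to be about 0.32, or about 0.39 to 0.40 at the Bonferroni level.

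**The case against.** - **Peak ALT is itself a primary outcome.** This stands. The sized statistic is one of the four, so the calculation is not irrelevant to the primary analysis. It does not extend to the other three by being one of them.
- **AUC may not be the sole deciding outcome.** This also stands. Outcome measures gives AUC that role, but Statistical analysis requires superiority on the primary outcomes and corrects for all four, so the peaks count too. The point does not depend on which reading is right: the power sentence covers AUC under both.
- **A reader might infer that the AUC comparison is underpowered.** The document does not support this. It gives no daily SDs, between-day correlations or effect duration. Assumed enzyme courses can put AUC power well below or well above 80%.
- **A reader might infer that the plan claims peak ALT is the limiting outcome of all four, or that its sample size arithmetic is wrong.** Neither is so. The comparison is with peak AST only, and the arithmetic is exact.
- **An AUC calculation may exist in the full protocol or analysis plan.** Possibly. But this is a stated figure attached to outcomes that the printed sizing does not cover, not a detail merely left out.
- **Recruitment, follow-up and unblinding are complete, so N cannot change.** True, and this limits the practical consequence to how power is stated and how results are read.

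**Conclusion.** The power sentence is too broad. The document supports 80% for peak ALT at an unadjusted one-sided 5% level with about 121 evaluable per group, and nothing wider. For the AUC of ALT and AST the figure is unsupported, in an unknown direction. Under the plan's own Bonferroni rule, peak ALT itself has about 59% power, so keeping an unqualified 80% for that outcome would still be wrong.

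These figures rest on the printed SD and difference for peak ALT, 10% dropout, a t test, and one-sided testing at 0.05/4. The AUC powers tabulated are illustrations over assumed effects and are not evidence of a deficit.

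**What to change.** - In Sample size and Statistical analysis, replace the group claim with a statement of 80% power for peak ALT at an unadjusted one-sided 5% level. Add that at the Bonferroni level of one-sided 0.0125 the power for peak ALT is about 59% with 121 per group.
- State that AUC was not sized. Give the standardised AUC effect detectable with 80% power at about 121 per group: about 0.32 SD at one-sided 5%, and 0.39 to 0.40 SD at one-sided 0.0125.
- Convert this to AUC units using an SD from the earlier 25-min trial, if daily values exist there; the article cites only peak summaries from it. Do not take the SD from this trial. Its data were unblinded on 16 July 2023, and Outcome measures says the primary outcomes were decided after that date.
- Report each AUC comparison as an estimate with its confidence interval, and do not describe a null AUC result as coming from an 80%-powered test.

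The cost is wording and at most one recalculation. Enrolment and procedures do not change. The downside is a less favourable stated power.

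### The 80% power claim for the primary outcomes ignores the four-way Bonferroni correction: on the protocol's own inputs, power for peak ALT is about 60% (65% with no dropout), and none is shown for the AUCs

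*Protocol article*

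**What the plan says.** The Sample size section of the protocol article plans for 270 patients: "with a total of 270 patients (135 within each group". Its inputs are a target difference of 58.882 IU/L and standard deviations given as "of the postoperative serum peak ALT value is 184.684, AST value is 141.1 between two groups". Peak ALT sets the number: "The sample size calculated using peak ALT value is larger than using peak AST value". The error rates are "to achieve an 80% statistical power (Uβ = 0.84, 1-sided test") and "at the 5% significance level (Uα = 1.645, 1-sided test"), with about 10% dropout.

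The Outcome measures section names four primary outcomes: peak ALT, peak AST, AUC of ALT and AUC of AST. It identifies the AUCs as the measure on which superiority will be claimed.

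The Statistical analysis section adds the testing rule: "Bonferroni correction will be performed to correct for four primary outcomes statistically". It exempts the primary outcomes from two-tailed testing and says the multiplicity adjustment was changed after 16 July 2023, which the Trial status section gives as the unblinding date. The same section states: "All included participants will provide 80% power to detect superiority with respect to the primary outcomes".

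**The concern.** The sample size and the test use different significance levels. The sizing calculation spends the whole one-sided 5% on one outcome. The testing rule divides that 5% among four. A stricter threshold with the same number of patients means lower power, yet the 80% figure stands unchanged beside the correction and is extended from one outcome to all the primary outcomes.

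What is at stake is how the results are read. If dexamethasone truly lowered peak ALT by the target difference, the trial would miss it about 40% of the time under the rule as written, not 20%. A reader relying on the printed 80% would give a non-significant peak ALT more weight than it deserves. For the AUCs, a reader would assume a planned power that the article does not show.

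**Working it through.** **Inputs.** From the Sample size section: σ = 184.684 (peak ALT), σ = 141.1 (peak AST), δ = 58.882, z for α = 1.645 (one-sided 5%), z for β = 0.84, dropout 10%, 135 per group. From Outcome measures and Statistical analysis: four primary outcomes, Bonferroni, primary tests not two-tailed.

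**1. Reproduce the plan's figure.**

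n per group = 2 (z_α + z_β)² (σ/δ)² = 2 × (1.645 + 0.84)² × (184.684/58.882)² = 121.5 evaluable.

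Allowing for dropout: 121.5/0.9 = 135.0 per group, as stated. The sample size therefore rests on peak ALT at the full one-sided 5%, with no allowance for multiplicity.

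**2. Level per outcome after the correction.**

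0.05/4 = 0.0125, one-sided; critical value z = 2.241.

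**3. Power for peak ALT at that level.**

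Standardised difference = 58.882/184.684 = 0.3188. The expected test statistic is 0.3188 × √(n/2), and power is Φ(expected statistic − 2.241).

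| Evaluable per group | Expected statistic | Power at one-sided 0.05 | Power at one-sided 0.0125 |
|---|---|---|---|
| 121.5 (10% dropout) | 2.485 | 80% | Φ(0.244) = 59.6% |
| 135 (no dropout) | 2.619 | 83.5% | Φ(0.378) = 64.7% |

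The noncentral t distribution gives nearly the same: 59.3% with 122 per group and 64.3% with 135.

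**4. Peak AST.** The section gives one difference and does not say outright that it applies to both enzymes. Assuming it does, the standardised difference is 58.882/141.1 = 0.4173. With 121.5 per group the expected statistic is 3.253, and power at 0.0125 is Φ(1.011) = 84%.

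**5. AUC of ALT and AST.** The article gives neither a standard deviation nor a target difference, so no power can be computed from it.

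**The case against.** The strongest reply is that the sentence does not define success. If it means superiority on at least one of the four outcomes, power cannot be lower than that of the best single outcome. That is about 84% for peak AST if the same difference is assumed, so 80% would be met. This shows that the sentence is ambiguous, but it does not rescue it. The only calculation in the article is for a single outcome at the full 5%, success is nowhere defined as any one win, and the 84% depends on a difference not clearly stated for AST.

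A second reply is that the sample size is presented as the original conception and came before the changed multiplicity rule. Recruitment closed on 1 April 2023 and the change came after 16 July 2023. That explains the mismatch and is openly disclosed. But the power statement stands in the current text beside the correction, with nothing to say it refers to the earlier basis.

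Third, 60% assumes that the full 10% is lost. This is fair: the figure should be given as 60% to 65%. The lower end is a reasonable planning value, because the section on follow-up and withdrawal says that withdrawn participants' data will not be analysed.

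Finally, a stricter level does not inflate false positives. That is right, and the point concerns stated power only.

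**Conclusion.** The 80% statement is wrong as written. At the one-sided 0.0125 level that the protocol's rule implies, power for peak ALT, the outcome that set the sample size, is about 60% after the planned dropout and about 65% with none. This uses the protocol's own standard deviation and difference, a one-sided family level of 5% split equally over four outcomes, and the normal approximation. For the AUCs, nothing shown supports the figure.

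A reader might infer three stronger things that the documents do not support:

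- **Every primary outcome falls short of 80%.** Under the assumed common difference peak AST does not, and for the AUCs the power is unknown, not shown to be low.
- **Power is lower still because the corrected tests are two-sided.** The protocol sizes one-sided and exempts the primary outcomes from two-tailed testing.
- **The trial as a whole has some particular power to win on any, or on all four, of the outcomes.** That needs correlations and AUC effects that the article does not give.

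**What to change.** In the Statistical analysis section, replace the 80% sentence with, for example:

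> The sample size was set for peak ALT at an unadjusted one-sided 5% level, before the multiplicity rule was changed after 16 July 2023. At the Bonferroni-adjusted one-sided level of 0.0125, power for peak ALT is about 60% with 10% dropout (65% with none). If the same 58.882 IU/L difference is assumed for peak AST, its power is about 84% with 10% dropout. No power was calculated for the AUC outcomes.

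If a power calculation for the AUCs does exist outside the article, the last sentence should give its inputs and result instead.

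The cost is this one change of text and a less favourable stated power. Recruitment is complete, so no extra patients are asked for, and no analysis changes.

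### The four primary outcomes are compared without the preoperative ALT and AST already collected, and the data decide whether each is tested on means or on ranks

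*Protocol article*

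**What the plan says.** Under Outcome measures the article lists four primaries: "Primary outcomes are as follows: peaks value of ALT and AST and AUC of ALT and AST". Peak is the highest value over the seven postoperative days, and "AUC is calculated by the value of postoperative 7 days". The same section states that "Preoperative laboratory parameters are viewed as baseline of postoperative laboratory parameters", and Data collection lists ALT and AST among the preoperative laboratory tests.

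Under Statistical analysis, "The AUC of ALT and AST will be tested for superiority, analyzed by" Student's t or the Mann-Whitney U test. The next paragraph covers all continuous variables, and so the peaks as well. They are summarised by mean or median "based on normality testing and compared by an independent sample" t test or the Mann-Whitney test. No covariate, change score or regression model is named for any primary outcome.

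The Sample size section works from a difference in mean peak ALT of 58.882 IU/L with a standard deviation of 184.684. Trial status dates the unblinding to 16 July 2023.

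**The concern.** There are two separate weaknesses.

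**Baseline is measured and then left out.** The preoperative value enters neither the outcome definitions (postoperative days only) nor the named tests. If it predicts the postoperative value, part of the residual variance could be removed with data already held, and a chance imbalance in preoperative ALT or AST would not pass straight into the estimate.

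**The primary comparison is not fixed.** For each of four outcomes the choice between a comparison of means and a comparison of ranks depends on how the data look. Strictly, the sentence attaches normality testing to the summary statistic. The natural reading is that it also picks the test. If it does not, the choice between the two tests has no stated rule. Either way, a reader cannot say in advance which quantity each primary result concerns. If Mann-Whitney is selected, the test no longer addresses the mean difference used for sizing. This matters more here because the article itself says that the primary outcomes and the multiplicity adjustment were settled or changed after 16 July 2023.

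**Working it through.** **Inputs from the Sample size section.** Target difference δ = 58.882 IU/L; σ, where the "postoperative serum peak ALT value is 184.684"; one-sided 5% level (1.645); 80% power (0.84); about 10% dropout; 1:1 allocation.

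**1. Reproduce the plan's figure.** n per group = 2 × [184.684 × (1.645 + 0.84) / 58.882]² = 121.5, so 122. Allowing for dropout, 122 × 1.10 = 134.2 (135) or 122 / 0.90 = 135.6 (136). The stated 135 is therefore reproduced, and it comes from an unadjusted one-sided comparison of means.

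**2. Effect of adjusting for baseline.** With correlation r between the preoperative and postoperative value, the residual SD is about σ√(1 − r²). The article does not give r, so it is assumed over a range. With 122 evaluable per group:

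(δ/σ) × √(122/2) = 0.3188 × 7.810 = 2.490

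Power = Φ[2.490/√(1 − r²) − 1.645]

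| Assumed r | 1 − r² | Power, one-sided 0.05 | n per group for 80% power, before dropout |
|---|---|---|---|
| 0 (plan as written) | 1.00 | 80.1% | 122 |
| 0.1 | 0.99 | 80.4% | 121 |
| 0.2 | 0.96 | 81.5% | 117 |
| 0.3 | 0.91 | 83.3% | 111 |
| 0.4 | 0.84 | 85.8% | 103 |
| 0.5 | 0.75 | 89.1% | 92 |

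For context only: at 0.05/4 = 0.0125 one-sided (2.241), unadjusted power is Φ(2.490 − 2.241) = 60%, and the same range of r gives 60% to 74%. The fall from 80% to 60% comes from applying Bonferroni without resizing. It is a separate matter and not a consequence of omitting baseline.

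These figures are for peak ALT on the original scale. The article gives no SD for either AUC, so the same calculation cannot be made for them.

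**3. Behaviour of the normality rule.** This was simulated with 3,000 runs per scenario, 122 per group, lognormal values with SD 184.684 and an assumed control mean of 250, 300 or 400 IU/L. Because the article names no normality test, Shapiro-Wilk at 5% in each arm was assumed.

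- The rule selected Mann-Whitney in every run.
- Its one-sided type I error was 0.044 to 0.053, and its power was no lower than that of the t test.
- Log-scale ANCOVA also held its level (0.044 to 0.053). Its power was 90–95% against 86–93% for Mann-Whitney at r = 0.3, and 94–98% against 85–93% at r = 0.5.

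The simulated data follow the log-linear form that the ANCOVA assumes, so this last comparison is favourable to it.

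**The case against.** The strongest reply is that nothing here is invalid. Allocation is randomised 1:1 and concealed, so the unadjusted comparison is unbiased, and the simulation found no inflation from the pre-test rule. The benefit of adjustment depends on an r that nobody can read from the article, and at 0.2 or less it is worth about one point of power. A supporting adjusted analysis may also exist in an analysis plan that is not shown. All of this stands. It limits the point to precision and to an unfixed comparison.

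A reader might infer more than the article supports:

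- *That the choice of test after unblinding inflates the error rate.* The article indicates a rule rather than a free choice, and on skewed data that rule behaved as if fixed.
- *That randomisation was unstratified and that cirrhosis, resection extent and surgical approach distort the result.* The article names no strata, but silence in a condensed account is not a statement that there were none. It nowhere says how strongly these factors affect transaminases. Extent and fibrosis are given planned subgroup analyses.
- *That adjustment would restore the power lost to Bonferroni.* A model introduced after unblinding cannot recover confirmatory power.

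It is also fair to say that a geometric mean ratio departs from the 58.882 IU/L difference just as a rank test does. The gain is that it is one stated quantity, with an interval, for all four outcomes.

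**Conclusion.** The point holds as a recommended improvement and not as an error of validity. The named tests ignore a baseline measurement the trial already has, and they leave each primary to be tested on means or ranks according to the data, although the design was built on means. For peak ALT at the design level, adjustment moves power from 80.1% to 80.4–81.5% for r of 0.1 to 0.2, to 83.3% at 0.3, and to 85.8–89.1% at 0.4 to 0.5. These gains rest on the assumed r, on 122 evaluable patients per group, and on a normal approximation on the original scale. They are not the exact power of a log-scale model. The mismatch between the test and the sizing quantity does not depend on r.

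**What to change.** - Use one analysis for all four primaries: ANCOVA of log(peak) or log(AUC) on arm and the log preoperative value of the same enzyme. Report the geometric mean ratio with an interval matched to the Bonferroni level (two-sided 97.5% if each outcome is tested at one-sided 0.0125).
- Drop the normality pre-test.
- Add other covariates only if their values were fixed before randomisation, for example preoperative liver disease status or the planned extent and approach. Data collection lists minor/major hepatectomy and open/laparoscopic under intraoperative parameters. As recorded there, they may reflect events after allocation and dosing and should not be used.
- State that the model was added after the unblinding of 16 July 2023, and report it beside one unadjusted test that is the same for all four outcomes.

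The cost is a little analysis time on data already held. There are two drawbacks. The effect becomes a ratio rather than the IU/L difference used for sizing, and the adjusted result is supportive rather than confirmatory.
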